### Participants

2.3

Patients who meet the inclusion criteria will be enrolled in the study. The inclusion criteria are as follows: (1) patients who are male sex and aged 18–45 years; (2) have a BMI less than 28 kg/m^2^; (3) are classified as ASA I-II; (4) undergo transurethral ureteral laser lithotripsy under quasi-general anesthesia, with an anesthesia time of 15–30 min; (5) have a no. 18 indwelling catheter after the operation; (6) are able to understand and willing to undergo evaluations related to CRBD as well as complete questionnaires; (7) sign the informed consent form voluntarily.

The exclusion criteria are as follows: (1) patients with serious heart, liver, kidney or other diseases; (2) patients with skin injuries, ulcers, sensory disturbances, acute closed injuries, suppurative infections or acute inflammation and other infectious diseases, skin diseases, severe diabetes, high fever with excessive product material at the superior margin of the pubic symphysis; and (3) patients with hypertrophy of the prostate, urethral stenosis, and a 1-year history of indwelling urethral catheters.

### Randomization and masking

2.4

An envelope lottery will be used to randomize patients into groups, and because the study will be conducted across 3 centers, stratified randomization is required, with 30 patients included from each center, 15 of whom will be assigned to the experimental group and the remaining 15 will be included in the control group. The study will be conducted in double-blinded manner, and patients were only informed that they were enrolled in a clinical trial for the prevention of postoperative CRBD and were assigned to a study group with a unique study number, and the specific grouping (experimental/control) and the differences in the composition of the hot compress bags (full dose/one-tenth dose of medicinal powder) were not disclosed to the patients at any stage before, during, or after the surgery. The hot compress will be placed over the patient’s pubic symphysis immediately after intubation under general anesthesia and removed 60 min after surgery by a site nurse who will not be involved in follow-up visits. Patients, anesthesiologists, surgeons, note-takers, data registrars and analysts will be unaware of the group assignments. The TCM package will be distributed to each center by the Department of TCM of Shanghai Fourth People’s Hospital. Both groups will emit the smell of TCM, which are indistinguishable by odor alone. Group assignments will be maintained by the personnel at the main site who are not involved in the study but rather responsible for the study group numbers and hot compresses. Only when the patient has a serious adverse reaction that is suspected to be related to the intervention itself will he or she be responsible for the emergency unblinding of the patient to ensure timely treatment of the condition.

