### Study design

2.1

This is a multicenter, randomized, parallel group controlled study. The study period is November 2024–November 2025. A 24-h observation period will be included in the study (pictured). Patients who provide written informed consent will be tentatively enrolled and screened for eligibility during the observation period. In the experimental group, a hot compress (40–45 °C) of a Xiao-Xu-Ming-Tang and salt mixture will be placed above the pubic symphysis immediately after intubation. In the control group, a hot compress (40–45 °C) of one-tenth of an improved Xiao-Xu-Ming-Tang (This dose was confirmed to be non-therapeutic for CRBD based on our pre-experimental data and clinical dosage principles, cannot produce a significant effect on relieving bladder discomfort) and sea salt mixture will be placed above the pubic symphysis. During the observation period, the severity of CRBD will be graded using a scoring system developed and used by Agarwal et al. (18). The severity of CRBD will be divided into 4 grades: grade 1, the patient reports no symptoms of urinary tract or bladder discomfort; grade 2, the patient reports mild urinary tract or bladder discomfort only after prompting; grade 3, the patient reports moderate urinary tract or bladder discomfort without prompting but does not exhibit any behavior alluding to the discomfort; and grade 4, the patient reports severe urinary tract or bladder discomfort. The behaviors alluding to discomfort included flailing limbs, a strong vocal response, and attempts to remove the catheter.

*Experimental group (Composition of the TCM formulation)*: 9 g Qianghuo, 9 g Chuanxiong, 9 g Huangqin, 6 g Mahuang, 9 g Muxiang, 9 g Prepared *Aconitum Carmichaelii* Radix, 6 g Fangji, 9 g Fangfeng, 6 g Yangchun Sha, 9 g Sheng Baishao (full dose of improved Xiao-Xu-Ming-Tang) are ground into powder, mixed thoroughly with 100 g coarse sea salt, packed into a breathable cloth bag, heated to 40–45 °C, and applied as a hot compress above the pubic symphysis immediately after intubation until 60 min after surgery.

*Control group*: one-tenth of the full dose of improved Xiao-Xu-Ming-Tang powder (the proportion of each medicinal material is consistent with the experimental group), mixed thoroughly with 100 g coarse sea salt, packed into a breathable cloth bag, heated to 40–45 °C, and applied as a hot compress above the pubic symphysis immediately after intubation until 60 min after surgery.

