#### Secondary outcomes

2.2.2

The five secondary outcomes are as follows: (1) the incidence of moderate-to-severe CRBD at 1 h, 6 h, and 24 h after surgery; (2) the NRS score, which is used to evaluate postoperative pain, at 30 min, 1 h, 6 h, and 24 h after surgery, with scores ranging from 0, indicating no pain, to 10, indicating the worst pain imaginable; (3) the incidence of skin discomfort above the pubic symphysis (scald, redness, pruritus, allergy, etc.); (4) vital signs (blood pressure, heart rate, and oxygen saturation) at 10, 20, 30, 40, 50 min, 1 h, 6 h, and 24 h after surgery; and (5) patient satisfaction [24 h after surgery, patient satisfaction using a 5-point scale, with items graded 1 (“very dissatisfied”) to 5 (“very satisfied”)].

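### Section 2.4 keeps from patients, permanently, that the arms receive different herbal strengths; masking does not need this, and it conflicts with the written informed consent stated elsewhere

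*Protocol article*

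**What the plan says.** Section 2.4 describes what patients are told: "patients were only informed that they were enrolled in a clinical trial for the prevention of postoperative CRBD", together with assignment to a study group under a unique number. It then names two things that are withheld. One is the patient's own grouping. The other is the contrast between the arms: "the differences in the composition of the hot compress bags (full dose/one-tenth dose of medicinal powder) were not disclosed to the patients". Both are withheld "at any stage before, during, or after the surgery". No later disclosure is described.

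Section 2.1 gives the control bag as "one-tenth of the full dose of improved Xiao-Xu-Ming-Tang powder", in the same herb proportions as the experimental bag and with the same 100 g of salt. It describes this dose as non-therapeutic for CRBD.

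Consent appears three times. Section 2.1 states: "Patients who provide written informed consent will be tentatively enrolled and screened for eligibility during the observation period". Inclusion criterion 7 in section 2.3 requires that patients "sign the informed consent form voluntarily". Section 2.8.1 has the form signed in the screening period.

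On skin reactions, the third secondary outcome in section 2.2.2 is "the incidence of skin discomfort above the pubic symphysis (scald, redness, pruritus, allergy, etc"), and note d to Table 1 lists allergies among the adverse events recorded. The skin-related exclusions in section 2.3 begin "patients with skin injuries, ulcers, sensory disturbances, acute closed injuries, suppurative infections or acute inflammation and other infectious diseases, skin diseases, severe diabetes". Neither those criteria nor the medical history itemised in note b to Table 1 mentions allergy or an earlier reaction to a component.

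**The concern.** A double-blind trial has to hide which arm a given patient is in. It does not have to hide that there are two different arms, or how they differ. Section 2.4 treats these as one secret. Followed as written, patients agree to take part without knowing that half of them receive a preparation that the investigators themselves regard as non-therapeutic, and they do not learn this afterwards. That is hard to square with consent described as informed.

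This is not a gap left by condensing a protocol into an article. The article states positively what patients are told and what they are not told. A fuller document that said otherwise would contradict section 2.4, and the two would still have to be brought into line.

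A second, smaller matter sits beside it. The plan expects that allergic skin reactions may occur and counts them as an outcome, but its listed eligibility and history items do not ask about known hypersensitivity.

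**Working it through.** There is no figure of the plan's own to reproduce here. The check compares sections, with simple arithmetic on the two bags.

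**1. Size of the undisclosed difference.** Inputs are the ten herb weights and the salt weight in section 2.1.
- Full dose: 9 + 9 + 9 + 6 + 9 + 9 + 6 + 9 + 6 + 9 = 81 g.
- Control dose: 81 / 10 = 8.1 g.
- Bag contents: 81 + 100 = 181 g against 8.1 + 100 = 108.1 g, a difference of 72.9 g.

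**2. Who is covered.** Sections 2.4 and 2.6 plan 3 × 30 = 90 patients, 45 per arm. The rule in section 2.4 makes no exception.

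**3. What masking needs.**
- Withholding the individual grouping is necessary for a blinded patient.
- Telling every patient that two strengths are compared 1:1 gives the same information to both arms. By itself it identifies no one's allocation.
- Withholding the existence of the contrast is therefore not part of what masking requires, and nothing in masking explains withholding it after the 24 h follow-up has ended.

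**4. Consent against non-disclosure.** Sections 2.1, 2.3 and 2.8.1 rely on written or signed informed consent. Section 2.4 says that the defining difference between the arms is not told to the patient at any stage. As written, the consent those sections rely on lacks the central fact about the comparison.

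**5. How far the wording reaches.**
- The express non-disclosure covers the differences in composition. It does not name the ingredients.
- Both arms contain the same ten herbs in the same proportions, so a single ingredient list could be given to all patients without revealing any difference.
- The word in section 2.4 that limits what patients were told cannot be read literally. Section 2.8.1 and note a to Table 1 show that patients also receive instruction on the NRS and on recognising CRBD.
- Ignorance of the herbs therefore does not follow from the text.

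**6. Allergy.** Allergy is listed as a possible harm in section 2.2.2 and in note d to Table 1. A hypersensitivity item appears neither in the exclusion criteria of section 2.3 nor in note b to Table 1, although both lists are fairly detailed about the skin at the compress site. Because the control bag holds the same herbs, the question concerns both arms.

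**The case against.** The strongest reply has four parts.

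**The consent form is not shown.** Written consent is stated repeatedly, and the form may describe more than section 2.4 suggests. This stands as a limit. A reader might infer that consent was in fact uninformed, or that patients did not know which herbs would be on their skin. The article does not support either as an established fact. What it supports is a conflict between its own sections.

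**The allergy point concerns something absent from a condensed article.** This largely stands too. A reader might infer that a patient with a known sensitivity would pass screening with no chance to say so. No sentence forbids asking about allergy, an investigator can ask whatever the patient knows about dose, and a full protocol may contain the question. What remains is a mismatch between a stated anticipated harm and two itemised lists that do not mention it.

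**Disclosure is not free for the blind.** A reader might infer that the secrecy protects nothing. That is too strong. The compress stays on until 60 min after surgery, so patients have it in place at the 30 min primary assessment, and the Discussion calls that outcome subjective. Section 2.4 claims that the bags cannot be told apart by odour, but says nothing about bulk, and the stated contents are 181 g and 108.1 g. A patient who knows of a tenfold difference could try to guess. This is a reason to match the bags. It does not justify withholding the comparison, least of all afterwards.

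**The study may be over.** Section 2.1 gives November 2024 to November 2025, and the article is dated April 2026. If that schedule held, a new consent form cannot reach these patients. This changes the remedy but leaves the conflict in place.

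**Conclusion.** The concern holds in a limited form. Section 2.4 states as a rule that patients are not told, even after surgery, that the arms receive different strengths of the herbal powder (81 g against 8.1 g). That goes beyond masking and conflicts with the informed consent in sections 2.1, 2.3 and 2.8.1. The rule covers all 90 planned patients.

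The conclusion rests on taking section 2.4 at its word and on the herb weights in section 2.1. It does not depend on what the unseen consent form says: if the form discloses the two strengths, section 2.4 is wrong; if it does not, the description of consent is.

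The matter is one of ethics and reporting. No bias in any estimate has been shown, and the number of patients with a relevant allergy is not given. The missing hypersensitivity item is a separate, lesser inconsistency.

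**What to change.** **Section 2.4.** Replace the non-disclosure statement with one along these lines: the consent information describes both compresses (full-dose and one-tenth-dose herbal powder with sea salt), their ingredients and the 1:1 random allocation; only the individual assignment is withheld until unblinding, and it is made available to patients afterwards.

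**If enrolment is complete.** State in the report what the consent form disclosed about the ingredients and the two strengths, notify the ethics committee, and debrief patients.

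**Allergy.** Reconcile section 2.2.2 and note d to Table 1, which anticipate allergic reactions, with section 2.3 and note b, which contain no known-hypersensitivity check. State whether it was asked about at screening.

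**Blinding.** Confirm that the two bags are matched in weight and appearance as well as odour, since their stated contents differ by 72.9 g.

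**Cost.** For a trial still enrolling: a revised consent text, a reconciled eligibility and history list, and ethics notification. Some patients may decline or be excluded, and some may try to guess their arm from the bag's bulk. For a completed trial: a correction to the text, a notification and a letter to patients.

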However, CRBD is difficult to prevent and treat. The main methods for preventing and treating CRBD include local anesthesia, psychological intervention and drug intervention. Currently, several methods have been proven to be effective for preventing CRBD, such as nerve block, transcutaneous electrical nerve stimulation, lidocaine, intravesical bupivacaine, magnesium sulfate, and nefopam (5–10). Because these methods are primarily implemented intraoperatively, the cost of the procedure increases. Thus, considering the substantial number of patients with indwelling catheters after surgery under general anesthesia, a cost-effective, feasible and effective strategy for preventing postoperative CRBD is needed. Traditional Chinese medicine (TCM) hot compresses have been used for more than 2,000 years. They can dilate local capillaries, improve blood circulation, reduce inflammation and swelling, dispel cold and dampness, alleviate pain and eliminate fatigue. TCM hot compresses offer a technically simple and cost-effective alternative (11, 12). TCM hot compresses can relieve pain and discomfort caused by muscle spasms as well as relieve breast tenderness and pain, post-stroke shoulder-hand syndrome and postpartum urinary retention (12–14). The improved Xiao-Xu-Ming-Tang powder is mixed with coarse sea salt (40–45 °C hot compress) to increase the skin permeability of the active components—the mild heat can dilate the suprapubic capillaries and open the skin stratum corneum pores, and the active compounds (volatile oils, alkaloids) of the medicinal materials are small molecular weight substances that can quickly penetrate the skin, enter the local subcutaneous tissue and bladder meridian, and exert anti-spasm and pain-relieving effects without systemic absorption (no systemic side effects) (15). [name], a renowned TCM expert in Shanghai, and his research team confirmed that Xiao-Xu-Ming-Tang can significantly alleviate catheter-induced bladder discomfort and irritation, as well as pain associated with urinary calculi (16). Based on clinical practice, our hospital’s TCM department optimized the original Xiao-Xu-Ming-Tang formula to form the improved version, which consists of *Notopterygii Rhizoma et Radix* (Qianghuo), *Chuanxiong Rhizoma* (Chuanxiong), *Scutellariae Radix* (Huangqin), *Ephedrae Herba* (Mahuang), *Aucklandiae Radix* (Muxiang), *Aconiti Radix Praeparata* (Zhi Fuzi), *Stephaniae Tetrandrae Radix* (Fangji), *Saposhnikoviae Radix* (Fangfeng), *Amomi Fructus* (Yangchun Sha), and *Paeoniae Radix Alba* (Sheng Baishao). The active components of these herbs have clear pharmacological effects on CRBD: *Notopterygii Rhizoma et Radix* contains volatile oils (e.g., ligustilide) and sesquiterpenoids that dilate local blood vessels and promote transdermal absorption, with its volatile components regulating the bladder meridian and relieving smooth muscle spasm; *Chuanxiong Rhizoma*, *Scutellariae Radix*, and *Ephedrae Herba* contain ephedrine (alkaloid) and volatile oils that inhibit M-cholinergic receptors of bladder smooth muscle and reduce involuntary contractions—the core pathological mechanism of CRBD—and their alkaloid components have good transdermal permeability, exerting local effects through the suprapubic skin; *Aucklandiae Radix* contains volatile oils (e.g., costunolide) for regulating qi and relieving spasm, with volatile components quickly penetrating the skin to act on local bladder meridians; *Amomi Fructus* contains volatile oils that soothe the bladder and relieve micturition urgency, with active components having high transdermal bioavailability on the lower abdominal skin. Most of these medicinal materials have a strong aromatic odor and good transdermal absorption properties; ground into powder and applied externally, they can regulate Zang-Fu organs and meridians to achieve the balance of yin and yang, which has been verified by relevant studies (17). CRBD falls under the categories of stranguria with urgency and abdominal pain in TCM, with its core pathogenesis being qi stagnation and meridian obstruction. Surgical trauma and catheter stimulation give rise to qi stagnation in the bladder meridian, which further induces bladder smooth muscle spasm. The modified Xiao-Xu-Ming-Tang is formulated based on the TCM therapeutic principles of regulating qi, unblocking meridians, and relieving spasm. The selected medicinal herbs target the bladder meridian in the lower abdomen, which accords with the standard TCM clinical practice of syndrome differentiation and treatment.

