#### Follow-up period: end of surgery to 24 h after surgery

2.8.3

NRS and RASS scores will be evaluated by a dedicated follow-up researcher at 30 min, 1 h, 6 h, and 24 h after surgery. CRBD grades and patient satisfaction scores will be recorded at the same postoperative time points. The researcher responsible for documentation will complete the CRF. Patients’ vital signs on admission to the PACU, intraoperative anesthetic agents, RASS, NRS, CRBD, and adverse events will be recorded in the electronic data system. The study timeline is presented in Table 1.

**Table 1 tab1:** Timetable of the study period.

Timepoint	Screening period (−2~−1 d)	Preparation period (−1~0 d)	Surgery period (0 d)	Follow-up period (after awakening until 24 h postoperatively)								
		T0		T1	T2	T3	T4	T5	T6	T7	T8	T9
Eligibility screen and informed consent	X											
General condition of the patient^a^	X											
Training^b^		X										
Vital signs^c^	X			X	X	X	X	X		X	X	X
Random allocation		X										
Hot compress												
The CRBD score						X				X	X	X
The NRS score						X				X	X	X
Adverse events record^d^												
Satisfaction of patients												

*T0, Before induction of anesthesia; T1, 10 min after awakening; T2, 20 min after awakening; T3, 30 min after awakening; T4, 40 min after awakening; T5, 50 min after awakening; T6, 1 h after awakening; T7, 6 h after awakening; T8, 12 h after awakening; T9, 24 h after awakening.

a Patients were educated about how to recognize CRBD (for example, suprapubic discomfort or burning with the urge to urinate) and how to distinguish them from surgical pain.

b Obtain the patient’s name, hospitalization number, age, medical history (whether there are the following conditions, serious heart, liver, kidney and other diseases; If the hot compress site has skin injury, ulcer, sensory disturbance, acute closed injury, suppurative infection or acute inflammation and other infectious diseases, skin diseases, severe diabetes, high fever and excessive use of product materials, it is not suitable for hot compress; Patients with prostatic hypertrophy, urethral stricture, and a history of indwelling catheter within 1 year.

c Blood pressure, heart rate, and oxygen saturation.

d Burns, redness, itching, allergies, etc.

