To ensure strict compliance with the measurement time points, the study procedures were optimized. The follow-up researcher will perform assessments at the ward or PACU exactly at the scheduled times. Vital signs will be documented by nurses at fixed time points, and all data will be entered into the electronic system with time stamps to guarantee accuracy and consistency. All researchers and nurses received uniform training to standardize assessment procedures and minimize human-related time-point deviations.

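### Masking is not stated for the bedside CRBD assessor or the recovery-room physician, the bags worn at the 30-minute grading are matched on odour only, and the grade 2/3 cut has no fixed order of questions

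*Protocol article*

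**What the plan says.** Section 2.4 makes a general statement, "The study will be conducted in double-blinded manner", and then lists six masked roles: "Patients, anesthesiologists, surgeons, note-takers, data registrars and analysts will be unaware of the group assignments". It adds three safeguards. The nurse who places and removes the compress takes no part in follow-up visits, the allocation is held by personnel outside the study, and the two bags are said not to be distinguishable by smell.

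Section 2.8.3 says who assesses: "NRS and RASS scores will be evaluated by a dedicated follow-up researcher at 30 min, 1 h, 6 h, and 24 h after surgery". For the primary endpoint the wording is passive: "CRBD grades and patient satisfaction scores will be recorded at the same postoperative time points". A later paragraph of that section adds: "The follow-up researcher will perform assessments at the ward or PACU exactly at the scheduled times". Completion of the CRF belongs to a separately described documentation researcher. Section 2.8.2 has the recovery-room physician manage and record moderate or severe CRBD.

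Section 2.2.1 places the primary endpoint (grades 3 and 4) at 30 min after surgery. Under 2.1 the bag is "applied as a hot compress above the pubic symphysis immediately after intubation until 60 min after surgery". In the same section, grade 2 means that "the patient reports mild urinary tract or bladder discomfort only after prompting", while grade 3 is moderate discomfort reported unprompted. Table 1 counts its 30-minute visit from awakening instead.

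**The concern.** The endpoint is a patient-reported symptom, which the Discussion concedes is subjective, and it is cut exactly where prompting enters the grade definition. The order in which the assessor asks and listens can therefore move a patient between grade 2 (no event) and grade 3 (event). No order of questioning is given.

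That matters most if the person at the bedside has an idea of the arm. The masked list is explicit, yet it does not name the role closest to the primary endpoint. The grading is also done while the study bag is on the patient. The bags differ in how much they contain, and the article claims a match in smell but says nothing about bulk, weight or appearance. It also says of the herbs: "Most of these medicinal materials have a strong aromatic odor". A hunch about the arm, combined with an unscripted prompt, would bias the one comparison on which the trial is judged.

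**Working it through.** **1. Roles, side by side**

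| Role | Task (section) | In the masked list of 2.4? |
|---|---|---|
| Follow-up researcher | NRS, RASS and scheduled assessments (2.8.3) | Not named |
| Documentation researcher | Completes the CRF (2.8.3) | Plausibly a note-taker |
| Recovery-room physician | Manages and records moderate or severe CRBD (2.8.2) | Not named, unless counted as an anesthesiologist |
| Nurse handling the compress | Places and removes it (2.4) | Not listed, but kept out of follow-up |

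That the follow-up researcher grades CRBD is an inference. The text gives this person the scheduled assessments, and CRBD shares the NRS time points, but no sentence names the CRBD grader.

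**2. Timing**

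On the 2.2.1 clock, grading is at 30 min and removal at 60 min after surgery, so the bag is in place with 60 − 30 = 30 min to run. On the Table 1 clock, grading is 30 min after awakening, and the bag is still on only if the patient wakes within 30 min of the end of surgery.

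**3. Bag contents (weights from 2.1)**

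- Herbs, full dose: 9 + 9 + 9 + 6 + 9 + 9 + 6 + 9 + 6 + 9 = 81 g.
- Experimental bag: 81 + 100 g salt = 181 g.
- Control bag: 8.1 + 100 g salt = 108.1 g.
- Ratio: 108.1 / 181 = 0.60, so the control bag is about 40% lighter.

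**4. The plan's own figures (2.6)**

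Inputs: 70% against 35%, two-sided α = 0.05, power 0.90, 1:1. The pooled-variance formula is n = [1.960·√(2·0.525·0.475) + 1.282·√(0.70·0.30 + 0.35·0.65)]² / 0.35² = 40.7, so 41 per arm against the stated 42. Allowing 5% loss, 42 / 0.95 = 44.2, so 45. The sample size reproduces, and this point does not change it.

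**5. Illustration of size (assumed misgrading)**

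Suppose there is no true effect: the event rate is 70% in both arms with 45 per arm. A fraction f of full-dose grade 3 patients is graded 2, always in that direction. If a share s of events is grade 3, the observed full-dose rate is 0.70·(1 − s·f). The rejection rate is the sum, over all pairs of event counts with uncorrected chi-square p < 0.05, of Bin(a; 45, 0.70)·Bin(b; 45, 0.70·(1 − s·f)).

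| f | s = 0.5: observed rate | s = 0.5: rejection | s = 1: observed rate | s = 1: rejection |
|---|---|---|---|---|
| 0 | 70.0% | 5.3% | 70.0% | 5.3% |
| 0.10 | 66.5% | 6.9% | 63.0% | 11.3% |
| 0.15 | 64.75% | 8.7% | 59.5% | 18.6% |
| 0.20 | 63.0% | 11.3% | 56.0% | 28.3% |

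The document gives neither s nor f. Both are assumptions.

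**The case against.** The strongest reply is that silence is not unmasking. No sentence says that the follow-up researcher or the recovery-room physician knows the arm. The trial is declared double-blind, allocation is held off-study, and bag handling is separated from follow-up. An article may list roles loosely: note-takers could include whoever records the grade, and anesthesiologists could include the recovery-room physician. All of this stands. A reader might infer from the list that double-blinding is lost for the primary endpoint, and the document does not support that inference.

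Further points also stand in part:

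- **Both arms wear a bag.** Its presence at grading reveals nothing by itself; only a perceptible difference between bags could. The article says that odour does not distinguish them (2.4, and again in 2.6), so the aromatic herbs are weak evidence. The open route is bulk or look, on which the text is silent.
- **The bag need not always be on at grading.** Table 1's clock leaves this open.
- **Asking first can move only grade 3 patients.** Grade 4 is severe discomfort, and the article describes overt behaviours such as attempts to remove the catheter. The 11–28% figures therefore hold only if every event is grade 3.
- **Prompting is partly a reliability issue.** It would exist under perfect masking. Assessor training with a pass requirement (2.1) and patient instruction (2.8.1) are already planned, and the grades also differ in severity (mild against moderate). Neither provision, as described, fixes the order of questions.

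**Conclusion.** The point holds as a cheap improvement to how the primary endpoint is protected. It does not show that the trial is unblinded, and the claim that double-blinding is lost should not be made.

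The masked list omits the probable CRBD grader and the recovery-room physician. On the after-surgery clock, grading takes place with the bag on. The contents are 181 g against 108.1 g with only odour stated to match, and the cut defining the endpoint turns on prompting with no stated sequence.

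The possible size is modest to material and is illustrative only. One-directional misgrading of 10–20% of full-dose grade 3 patients takes the false-positive rate from about 5% to about 7–11% if half of events are grade 3, and to 11–28% in the limiting case where all are. These figures rest on a 70% rate in both arms, 45 per arm and an assumed degree of bias. That the follow-up researcher grades CRBD is itself inferred.

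**What to change.** 1. During grading, keep the bag under an identical opaque cover in both arms, and let only the site nurse who places and removes it handle or uncover it.
2. In the assessor training already planned, fix the order of grading: record any spontaneous complaint first, then ask one set question. This reduces the assessor's influence on grade 2 versus 3 but does not remove it.
3. In 2.4, name the CRBD assessor, the recovery-room physician and the nurses who record outcomes as masked. In 2.8.3, say who grades CRBD.
4. Reconcile the 30-minute clock, which runs from surgery in 2.2.1 and from awakening in Table 1, so that it is clear whether the compress is in place at the primary grading.

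The cost is protocol wording, a cover and a short script. No extra staff are needed and the sample size does not change. The downside is slightly more handling discipline in the PACU.
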